#### Secondary outcomes – students

Student wellbeing will be measured using the WEMWBS, and psychological distress using the Strengths and Difficulties Questionnaire (SDQ), using a self-report questionnaire administered during class time. The WEMWBS has been validated among teenagers from thirteen years [36], and the SDQ is a widely used measure among this age group, with well-established norms for a UK population [37]. It is a 25-item scale measuring emotional and behavioural difficulties, with a self-report version for 11–16 year olds. Student attendance for all year groups (total %) and attainment for year 11 students (% achieving five or more GCSEs grades 5–9 including English and Maths) will be measured using routine school census data published online.

WEMWBS, SDQ, attendance and attainment will all be measured as continuous variables.

A logic model hypothesising the mechanisms by which the intervention will have an impact on the primary and secondary outcomes is shown in Fig. 1.

**Fig. 1 Fig1:**
[figure not shown]
Logic Model of the WISE intervention

### Participant retention and loss to follow up

In the pilot study missing outcome data was largely due to participants not being present during data collection sessions. In this study we have built in time after the initial data collection sessions to follow up missing participants. Where possible second data collection sessions will be planned with students. It will be harder to ask schools to set aside more than one staff meeting for data collection, so teachers absent from the data collection session will be followed up by email and given the option of completing either an online survey or posting a paper one back to the study team. A certain number of participants will be lost to follow up due to leaving the school between baseline and follow up. For this reason our primary analysis will use a repeated measures design that includes all participants with any data (see below).

### Data management

Outcome data will be entered onto REDCap (Research Electronic Data Capture). Checks will be built into the database to disallow entry of impossible values. A randomly selected 10 % of the questionnaires entered will be checked by a second person to ensure data quality. Only the study team will have access to the final trial dataset. Information about each school and personal data from participants (names and teacher emails) will be stored in a database on a networked drive that is password protected and only accessible by the study team.

### Sample size calculation

The study is powered to detect a mean change of 3 points on the primary outcome - the WEMWBS score among teachers. This difference has been chosen as the minimum meaningful change discussed in a WEMWBS user guide [38]. A change of 3 points is also close to the difference in mean baseline scores between the highest and lowest ranked schools in the pilot study. Sample sizes were calculated using the clustersampsi command within Stata, which accounts for the clustered nature of the data by including intracluster correlation coefficients (ICCs) in the calculation. Based on the pilot data [34] we assumed a WEMWBS ICC of 0.01 (0.00, 0.05), a mean of 50 teachers followed up per school (with a coefficient of variation of sample size of 0.5), and a standard deviation for WEMWBS of 8.4. A sample size of 24 schools (12 intervention and 12 control) will achieve 83 % power at the 5 % significance level for an ICC of 0.05 (the highest of the confidence intervals in the pilot ICC); this would rise to 98 % for an ICC of 0.02.

### Statistical analysis

All statistical analyses will take account of clustering by school and repeated measures using random effect or robust standard errors for clustering and random effects for repeated measures. Analyses will be conducted using Stata (version 13 or higher). An intention to treat analysis will be applied.

#### Primary analysis

Repeated measures (random effects) models will be used to examine pattern of change in the primary outcome (teacher WEMWBS as a continuous measure) over baseline, one year and two year follow ups adjusted for stratification variables and additional appropriate variables. The models will include every teacher who has at least one measure (at baseline or either of the two follow-up periods), and are robust to data which are missing at random (MAR). Thus no imputation is needed for this analysis [39, 40]. Results will be presented as mean differences in the primary outcome between the trial arms, with 95 % confidence intervals and *p*-value.

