### Randomisation

Allocation will take place after baseline measures have been collected, and will be conducted by the study statistician, blinded to any identifying information. The statistician will randomly allocate schools stratified by geographical area and FSM scores (see Table 1) to intervention or control arm, using computer-generated random numbers.

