#### Secondary analyses

Analysis will include, linear (continuous outcomes), multinomial (ordinal outcomes) and logistic (binary outcomes) regression models depending on the outcome measure. They will be used to compare the outcome at follow up by arm, initially unadjusted for variables (accounting for clustering), then adjusted for baseline outcome and for school-level FSM and geographical area, as stratifying variables [41]. Then finally adjusted for important covariates such as age, gender and any other covariates that are not balanced at baseline.

For individual level outcomes that are measured at 12 and 24 months (e.g., PHQ-8), repeated measures models will be used, including a random effect for each individual, and random effects to allow for clustering by school. All individuals with at least one observation of the outcome measure will be included in the model for that outcome measure, under a Missing at Random (MAR) assumption.

For individual level outcomes that are only measured at 24 months (e.g., student WEMWBS), a regression will be used, with robust errors to account for clustering.

For school level outcomes that are measured at both 12 and 24 months (e.g., teacher absence), repeated measures models will be used. For outcomes at school level which are only measured at 24 months (e.g., student attainment), a simple regression will be used.

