#### Tests for interactions

Using appropriate interaction terms, we will test whether any effects of the intervention on teacher WEMWBS and PHQ-8 score differ according to: baseline teacher wellbeing/depression score (grouped as above or below the bottom quartile of the WEMWBS, or with a score of 10 or more on the PHQ-8), gender, geographical area (Wales/England) and school-level FSM. In the pilot less than 6 % of teachers selected an ethnicity other than white, and so ethnicity will not be considered in these analyses. We will look at the interaction between time and intervention, to test if the intervention had different effects at different time points. The effect of the intervention on student WEMWBS and SDQ score will be tested for interaction with baseline student wellbeing/SDQ score (grouped as above or below the bottom quartile of the WEMWBS and a score of 16 or more on the SDQ), gender, ethnicity, FSM eligibility, geographical area, and school level FSM. P-values will be interpreted with caution due to the low power and number of interactions being tested (e.g., we will use Bonferroni corrected or permutation *p*-values).

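### As worded, the primary model can average the pre-allocation baseline into the arm effect, and the text does not say which follow-up contrast is primary

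*Protocol article*

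**What the plan says.** Under Primary analysis, the protocol article fits random-effects models to teacher WEMWBS across baseline and both annual follow-ups, to look at the pattern of change. On who is included: "The models will include every teacher who has at least one measure (at baseline or either of the two follow-up periods". On what is reported: "Results will be presented as mean differences in the primary outcome between the trial arms", with a confidence interval and p-value. Neither a time point nor a model term is attached to that difference.

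Under Randomisation: "Allocation will take place after baseline measures have been collected".

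The only mention of an arm-by-time term is under Tests for interactions: "We will look at the interaction between time and intervention, to test if the intervention had different effects at different time points". It stands beside the subgroup tests, in a paragraph that ends by asking for caution with p-values because power is low and the tests are many.

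Under Sample size calculation: "The study is powered to detect a mean change of 3 points on the primary outcome". The inputs include "a standard deviation for WEMWBS of 8.4" and "a mean of 50 teachers followed up per school (with a coefficient of variation of sample size of 0.5".

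Under Secondary analyses, models are to be adjusted for the baseline value of the outcome. For outcomes measured at both 12 and 24 months, such as PHQ-8: "All individuals with at least one observation of the outcome measure will be included in the model for that outcome measure".

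**The concern.** A teacher with only a baseline score can contribute to the model only if baseline WEMWBS is a response. That is not an error in itself. What matters is how arm enters. Because schools are allocated after baseline, the expected arm difference at baseline is zero. If arm is a single effect common to all three occasions, that zero is averaged with the two follow-up differences and the headline estimate is pulled towards no effect.

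The text can be read that way. It reports one unqualified arm difference, and it keeps any variation of the effect over time for a separate interaction test. At stake is whether a true effect equal to the trial's own minimum meaningful change would be reported as such, and whether the stated power applies to the model that is fitted.

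**Working it through.** **Inputs from the protocol (Sample size calculation).** Difference 3 points; SD 8.4; 12 schools per arm; mean 50 teachers followed up per school; coefficient of variation (CV) of cluster size 0.5; 5% significance, taken as two-sided; ICC 0.05 and 0.02.

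**Assumptions (not in the protocol).** Within-teacher correlation over time ρ = 0.4 to 0.8; school effect constant over time; leaver rates as stated in step 2.

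**Step 1: reproduce the stated power.** Design effect DE = 1 + [(1 + CV²)·m − 1]·ICC; SE = SD·√(2·DE/(12·50)); power from a non-central t with 22 degrees of freedom.

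- ICC 0.05: DE = 1 + (62.5 − 1)(0.05) = 4.075; SE = 0.979; power 83.4% (stated 83%).
- ICC 0.02: DE = 1 + (61.5)(0.02) = 2.23; SE = 0.724; power 97.7% (stated 98%).

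The stated figures are therefore for a full 3-point difference at a single follow-up occasion.

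**Step 2: what a single arm effect estimates.** Take a model with time fixed effects, random intercepts for school and teacher, and one arm term. With complete data, the generalised least squares expectation of the arm term is (d0 + d1 + d2)/3, where d0 = 0.

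- True effects 3 and 3: (0 + 3 + 3)/3 = 2.0.
- True effects 1.5 and 3: (0 + 1.5 + 3)/3 = 1.5.
- Effects 3 and 3, with 5 of 50 teachers lost each year and not replaced: 1.83, 1.80 and 1.78 for ρ = 0.4, 0.6 and 0.8, so about 1.8.

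**Step 3: power of that estimate, complete data, true effects 3 and 3.** The variance is (2/12)·SD²·[ICC·(1 + CV²) + (ρ − ICC)/50 + (1 − ρ)/150], with (2/12)·8.4² = 11.76. For example, with ICC 0.05, ρ = 0.4 and equal school sizes (CV 0): 11.76·(0.05 + 0.007 + 0.004) = 0.717, so SE = 0.847. An expected estimate of 2.0 then gives 61.7% power.

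| ICC | School sizes | SE (ρ 0.4 to 0.8) | Power | Stated |
|---|---|---|---|---|
| 0.05 | equal | 0.847 to 0.883 | 62% to 58% | 83% |
| 0.05 | CV 0.5 | 0.930 to 0.963 | 54% to 51% | 83% |
| 0.02 | equal | 0.610 to 0.659 | 88% to 83% | 98% |
| 0.02 | CV 0.5 | 0.656 to 0.702 | 83% to 78% | 98% |

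As a cruder check, a 2-point difference with the SEs of step 1 has power 49.7% (ICC 0.05) and 75.2% (ICC 0.02). Together these give roughly 50–62% at ICC 0.05.

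**Step 4: the alternative reading.** If arm acts only after baseline, the expected estimate for effects of 3 and 3 is 3.0, with or without turnover. For effects of 1.5 and 3, a common post-baseline effect is (1.5 + 3)/2 = 2.25, against 1.5 at year 1 and 3 at year 2. The bias is gone, but the answer depends on which of the three is reported.

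**The case against.** The strongest objection is that nowhere does the article write arm as one constant term over three occasions. A stated interest in the pattern of change fits an arm effect that starts after baseline at least as well. There is no intervention before allocation, so a test of whether effects differ between time points is most naturally year 1 against year 2. That would presuppose an effect that already excludes baseline. This stands: a reader might infer that the reported effect will certainly be diluted to two thirds, and the document does not support that. The dilution is conditional on one reading.

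A second objection is that model coding belongs in the analysis plan, which is not shown. This stands in part. The point, however, is not a missing formula. The article itself sets the responses, the inclusion rule, the reported quantity and the place of the time term, and together these admit a biased estimator as a literal reading. The bold type that marks the primary outcome in Table 2 is lost in the text available and may settle the time point.

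Third, ICC 0.05 is the upper confidence limit from the pilot, whose estimate was 0.01. The power loss is smaller at ICC 0.02, as the table shows. The bias in the estimate does not shrink with the ICC.

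A reader might also infer that the PHQ-8 models contradict themselves by using baseline both as covariate and as response. That does not follow if at least one observation means a follow-up observation, which the wording allows.

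**Conclusion.** The concern holds as a conditional one. The primary analysis puts a pre-allocation measurement among the responses, reports an arm difference without a time point, and mentions arm-by-time only among the interaction tests. Fitted with one arm effect over all occasions, it would be expected to report a true 3-point effect as about 2.0, or about 1.8 with some 10% unreplaced leavers a year, and an effect building from 1.5 to 3 as about 1.5. Power for 3 points would be roughly 50–62% at ICC 0.05. At ICC 0.02 it would be about 83–88% with equal school sizes, and about 5 points lower once the planned size variation is included.

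The power figures rest on complete data, the assumed within-teacher correlations and a school effect constant over time. The 2.0 and 1.5 need only complete data and random intercepts. Under the other permitted reading there is no dilution, but the primary contrast is still not fixed in the text. Either way the wording should be settled before the analysis.

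**What to change.** State the primary model with baseline, year 1 and year 2 WEMWBS as responses, one common baseline mean for both arms, and separate arm effects at year 1 and year 2. Name one post-baseline contrast as primary, for example the two-year difference unless Table 2's bold already fixes another, and report the other as secondary. The year 1 against year 2 comparison can stay among the interaction tests.

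For teacher PHQ-8, use the same form, or say that the models require a follow-up observation and take baseline as a covariate.

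Under the common-baseline model every teacher with any measure stays in. No data or participants are added; the cost is a few lines of analysis wording.

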#### Secondary analyses

Analysis will include, linear (continuous outcomes), multinomial (ordinal outcomes) and logistic (binary outcomes) regression models depending on the outcome measure. They will be used to compare the outcome at follow up by arm, initially unadjusted for variables (accounting for clustering), then adjusted for baseline outcome and for school-level FSM and geographical area, as stratifying variables [41]. Then finally adjusted for important covariates such as age, gender and any other covariates that are not balanced at baseline.

For individual level outcomes that are measured at 12 and 24 months (e.g., PHQ-8), repeated measures models will be used, including a random effect for each individual, and random effects to allow for clustering by school. All individuals with at least one observation of the outcome measure will be included in the model for that outcome measure, under a Missing at Random (MAR) assumption.

For individual level outcomes that are only measured at 24 months (e.g., student WEMWBS), a regression will be used, with robust errors to account for clustering.

For school level outcomes that are measured at both 12 and 24 months (e.g., teacher absence), repeated measures models will be used. For outcomes at school level which are only measured at 24 months (e.g., student attainment), a simple regression will be used.

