#### Secondary outcomes – teachers

Teacher depression, absence and presenteeism will be measured within the same self-report questionnaire. Depression will be measured using the 8 item Patient Health Questionnaire (PHQ-8) [5]. The PHQ-8 is suitable for measuring levels of depressive symptoms in population-based studies and is short enough to be used in self-report surveys. Unlike the 9-item version it does not contain a question about thoughts of self-harm – due to such a low number of participants in the pilot reporting suicidal thoughts, it was decided that measuring suicidality as an outcome was not necessary. Sickness absence and presenteeism during the last 4 weeks will be measured using questions adapted from the Work Productivity and Activity Impairment questionnaire (WPAI) [35]. Teacher absence days, retirement and resignations will also be measured at one and two years using routine data collected by schools.

Teacher PHQ-8 will be measured as continuous variable, and as an ordinal variable (a score of 0–4 indicating no depressive symptoms/5–10 indicating mild symptoms/10–14 indicating moderate symptoms/15–19 indicating moderately severe symptoms 20–24 indicating severe symptoms) and a binary variable, with a cut-point of 10 or more indicating depression [5]. Teacher absence and presenteeism will be treated as binary (any vs no absence in the previous four working weeks and health problems having 0 effect vs 1–10 effect on work over the previous four working weeks), and each variable will also be categorised and treated as ordinal, to examine whether the intervention has a differential effect on increasing levels of absence and presenteeism. Teacher absence, retirement/resignation and student attendance and attainment as reported by schools, will all be reported as a school level %.

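### The five ordered PHQ-8 bands are assigned to multinomial regression, which ignores their order and yields four arm odds ratios with no single effect

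*Protocol article*

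**What the plan says.** The protocol article, Secondary outcomes – teachers, sets the scale of each outcome. "Teacher PHQ-8 will be measured as continuous variable, and as an ordinal variable" introduces five ordered severity bands, and the same sentence adds "a binary variable, with a cut-point of 10 or more indicating depression". Self-reported absence and presenteeism are each dichotomised, and in addition "each variable will also be categorised and treated as ordinal". For those two outcomes a purpose is given: "to examine whether the intervention has a differential effect on increasing levels of absence and presenteeism". The number of absence and presenteeism categories is not stated.

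Under Secondary analyses, the models are matched to outcome type: "linear (continuous outcomes), multinomial (ordinal outcomes) and logistic (binary outcomes) regression models". For individual outcomes measured at 12 and 24 months, with PHQ-8 as the example, that section calls for repeated-measures models with random effects for person and school. No ordered model (proportional odds or similar) is named anywhere in the article.

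**The concern.** The declared scale and the named model do not match. A multinomial model treats its categories as labels: put the bands in any other order and the fit is the same. With J categories it estimates J − 1 arm coefficients, so the five PHQ-8 bands produce four odds ratios against a reference band. None of them summarises whether the intervention moved teachers towards milder symptoms. Each adjustment covariate also takes four coefficients.

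At stake is the usefulness of the banded analysis. A consistent but moderate shift could appear as four imprecise odds ratios, with a joint test weaker than one that uses the order. For PHQ-8 the protocol gives no reason for accepting this, because the stated interest in effects at different levels is attached to absence and presenteeism only.

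**Working it through.** **1. The plan's own power figure.** Inputs from Sample size calculation: 3-point difference, SD 8.4, mean of 50 teachers per school, coefficient of variation 0.5, 12 schools per arm, 5% significance (two-sided assumed).

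Design effect = 1 + ((CV² + 1)m − 1) × ICC = 1 + (1.25 × 50 − 1) × ICC = 1 + 61.5 × ICC. Effective n per arm = 12 × 50 / design effect.

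| ICC | Design effect | Effective n per arm | Power, t with 22 df | Protocol |
|---|---|---|---|---|
| 0.05 | 4.075 | 147 | 83.4% | 83% |
| 0.02 | 2.23 | 269 | 97.7% | 98% |

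The stated figures reproduce. They concern teacher WEMWBS only; no power is given for any ordinal outcome.

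**2. Cost of the extra degrees of freedom under a common shift.** Take an effect for which a one-coefficient ordinal test has 80% power. Its noncentrality is (1.960 + 0.842)² = 7.85. Under proportional odds, a joint test of all J − 1 multinomial arm coefficients has approximately the same noncentrality spread over J − 1 degrees of freedom. Power is P(χ²(J − 1, 7.85) > 5% critical value).

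| Categories | df | Critical value | Power | Noncentrality for 80% | Sample-size ratio |
|---|---|---|---|---|---|
| ordered model | 1 | 3.84 | 80.0% | 7.85 | 1.00 |
| 3 | 2 | 5.99 | 70.9% | 9.63 | 1.23 |
| 4 | 3 | 7.81 | 64.5% | 10.90 | 1.39 |
| 5 | 4 | 9.49 | 59.5% | 11.94 | 1.52 |

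The last row is the PHQ-8 case. The rows for 3 and 4 categories are illustrative, since the absence and presenteeism levels are not stated.

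**3. A worked example at the trial's size.** Assumed control distribution over the five bands: 50 / 30.6 / 12 / 5 / 2.4%. Its top three bands sum to 19.4%, the pilot share scored moderately to severely depressed (on PHQ-9); the split is an assumption. A common odds ratio of 1.5 gives 60.0 / 26.2 / 8.8 / 3.4 / 1.6%. With ICC 0.02, n = 269 per arm:

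- Multinomial: noncentrality = (n/2) Σ (p − q)² / p̄ = 5.91 on 4 df, where p and q are the band shares in the two arms and p̄ is their mean. Power 46%.
- Proportional odds: variance of the log odds ratio = 1/36.2 (Whitehead formula), so z = ln 1.5 × √36.2 = 2.44. Power 68%.

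A simulation with 20,000 replicates at n = 268 per arm gave 46.9% and 67.9%. Over odds ratios of 1.3 to 1.75 and ICCs of 0.01 to 0.05, the loss was about 7 to 22 points with five levels, 5 to 18 with four and 4 to 11 with three.

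**4. When the effect is not a common shift.** Same control distribution, n = 268 per arm, two assumed intervention distributions:

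| Intervention arm (%) | Multinomial | 1-df ordinal |
|---|---|---|
| 50 / 36.6 / 8 / 4 / 1.4 | 38% | 10% |
| 43 / 43 / 10 / 3 / 1 | 75% | 9% |

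The ranking reverses.

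**The case against.** The strongest reply concerns absence and presenteeism. The protocol wants to know whether the effect differs across increasing levels of these outcomes. A multinomial model estimates level-specific effects directly, whereas a proportional-odds model assumes them equal. That stands: the choice is defensible for those two outcomes, though it still discards the order. A reader might infer that the protocol uses the wrong model for all three outcomes; the text does not support that.

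Second, PHQ-8 is also analysed as a continuous score, which uses the order of the full scale and gives one effect, and as a binary variable. A general shift need not be missed because the banded analysis is weak. This also stands. It limits the harm but does not give the banded analysis an interpretable result. For absence and presenteeism the companion analysis only separates any from none, so the ordinal model is the one self-report analysis that uses severity.

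Third, a reader might infer a large loss of power in general. The documents do not support this. The 80% reference is chosen for illustration, the protocol does not specify a joint test, and step 4 shows the opposite ranking for some effects.

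Finally, a reader might expect the top PHQ-8 bands to be too sparse to fit. The article gives no band distribution beyond the pilot's 19.4%, so this cannot be shown.

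**Conclusion.** The point holds in limited form, mainly for the PHQ-8 bands. The model named does not treat them as ordinal and returns four arm contrasts without a summary effect; that follows from the text without any assumption. The power cost, from 80% to about 60%, is conditional on a common shift and a joint 4-df test. The worked example further assumes a two-sided 5% test, the band distribution, the odds ratio and the WEMWBS ICC range, and it uses one time point without the gain from baseline adjustment or repeated measures. The outcomes affected are secondary and the primary analysis is untouched.

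**What to change.** For the PHQ-8 bands, name an ordered logistic (proportional-odds) mixed model with random effects for person and school. Report one common odds ratio with its 95% CI, check proportionality, and keep a partial proportional-odds or multinomial model as a supporting analysis.

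For absence and presenteeism, keep a level-specific model because the protocol asks a level-specific question. A partial proportional-odds (generalised ordered) model is preferable, since it uses the order; report the common odds ratio alongside it.

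The cost is a change of analysis wording, plus the need to check the proportional-odds assumption. No change to data collection or sample size is involved.

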### Outcome measures

The outcome measures will be collected at baseline and at the one year follow up (teacher outcomes only) and two year follow up (teacher and student outcomes). Baseline and outcome data will be collected during the final term of the academic year in each case. Table 2 shows the outcomes to be collected at each time point (primary outcome is in bold).

**Table 2 Tab2:** Outcomes to be collected by time point

	Baseline	Year 1	Year 2
Teacher	WEMWBS PHQ-8 Presenteeism Teacher absence (past 28 days) Teacher absence (%) [school level] Teacher retirements and resignations [school level]	WEMWBS PHQ-8 Presenteeism Teacher absence (past 28 days) Teacher absence (%) [school level] Teacher retirements and resignations [school level]	WEMWBS PHQ-8 Presenteeism Teacher absence (past 28 days) Teacher absence (%) [school level] Teacher retirements and resignations [school level]
Student	WEMWBS SDQ Attendance (%) [school level – all year groups] Attainment (%) [school level - year 11]		WEMWBS SDQ Attendance (%) [school level - all year groups] Attainment (%) [school level - year 11]

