#### Missing data

In the pilot study, missing data for teacher WEMWBS score was 1.6 % at baseline and 3.5 % at follow up, and for teacher PHQ-9 score was 7.4 % at baseline and 5.4 % at follow up. Missing data for student WEMWBS was 14.8 % at baseline and 10.9 % at follow up, and for student SDQ was 16.2 % at baseline and 12.7 % at follow up.

We will assess the impact of missing data and non-response on teacher WEMWBS and PHQ-8 outcomes and student WEMWBS and SDQ outcomes using an appropriate imputation model. If multiple imputation is used [42], imputation models will include all outcomes (baseline and follow-up), intervention arm, stratifying variables and a random effect for schools to allow for clustering, as well as any appropriate baseline covariates and interactions (see below). All secondary analyses will be repeated on the imputed datasets, and results combined using Rubin’s rules. We will also use sensitivity analyses to examine the impact of potential missing not at random (MNAR), by assuming that those with missing outcome scores had better/worse outcomes than equivalent individuals with complete data [43]. We will examine the sensitivity of our conclusions to missing outcome scores that are 20, 50 and 100 % SD worse than expected had they not been followed up, and similarly 20, 50 and 100 % SD better. We will also estimate the largest amount that would need to be added to/subtracted from imputed outcomes without changing the clinical interpretation of the trial.

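### In a default fit, the baseline-adjusted student regressions drop followed-up students who have no baseline score; for teacher PHQ-8, the plan must say how baseline enters if its one-observation rule is to hold

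*Protocol article*

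**What the plan says.** Under Secondary analyses, the protocol article compares outcomes at follow-up by arm in three steps. The first is "initially unadjusted for variables (accounting for clustering"). The second is "then adjusted for baseline outcome and for school-level FSM and geographical area, as stratifying variables". The third adds further covariates.

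The same section then divides individual-level outcomes by when they are measured:

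- **Teacher questionnaire outcomes.** "For individual level outcomes that are measured at 12 and 24 months (e.g., PHQ-8), repeated measures models will be used". The inclusion rule belongs to this paragraph: "All individuals with at least one observation of the outcome measure will be included in the model for that outcome measure". It rests on data being missing at random.
- **Student outcomes.** "For individual level outcomes that are only measured at 24 months (e.g., student WEMWBS), a regression will be used". Clustering is handled through robust standard errors. No inclusion rule is given.

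Outcome measures confirms that students have no one-year measure; data come at baseline, then "one year follow up (teacher outcomes only) and two year follow up (teacher and student outcomes").

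Missing data gives the pilot rates. On wellbeing it says "Missing data for student WEMWBS was 14.8 % at baseline and 10.9 % at follow up". The SDQ rates come next: "for student SDQ was 16.2 % at baseline and 12.7 % at follow up". For teacher PHQ-9 they were 7.4 % and 5.4 %. That section plans an imputation model for teacher WEMWBS and PHQ-8 and for student WEMWBS and SDQ. If multiple imputation is the method chosen, the model includes baseline and follow-up outcomes, and all secondary analyses are repeated on the imputed data.

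**The concern.** A regression with baseline on the right-hand side needs a baseline value for every person in it. Standard software silently omits anyone who lacks one. The unadjusted student model would therefore use every student with a 24-month score, and the adjusted models would use a smaller group. A reader comparing the two estimates could not tell covariate adjustment from a change of sample. Students who were in randomised schools and were followed up would be lost for want of a covariate measured before allocation.

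For teachers the issue is consistency of the text. If baseline PHQ-8 is a covariate, a teacher with a follow-up score but no baseline score cannot enter the adjusted model. A teacher with only a baseline score adds nothing to a model of follow-up outcomes. Either case breaks the promise to include everyone with at least one observation.

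**Working it through.** The plan states no figure for this loss, so there is none to reproduce.

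**Inputs.** Pilot missingness from Missing data: student WEMWBS 14.8 % at baseline and 10.9 % at follow-up; student SDQ 16.2 % and 12.7 %; teacher PHQ-9 7.4 % and 5.4 % (standing in for PHQ-8). Study population gives about 150 year 8 students per school and 24 schools, so about 3,600 students. Two assumptions are added: each pair of pilot percentages shares one denominator, and the pilot rates carry over.

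**Share of followed-up people with no baseline score.** Let b be the proportion missing at baseline and f the proportion missing at follow-up.

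- Independent waves: share = b.
- Greatest overlap (as many as possible miss both waves): share = (b − f)/(1 − f) when b > f.
- Least overlap (nobody misses both): share = b/(1 − f).

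| Outcome | Independent | Greatest overlap | Least overlap |
|---|---|---|---|
| Student WEMWBS | 14.8 % | (0.148 − 0.109)/0.891 = 4.4 % | 0.148/0.891 = 16.6 % |
| Student SDQ | 16.2 % | (0.162 − 0.127)/0.873 = 4.0 % | 0.162/0.873 = 18.6 % |
| Teacher PHQ | 7.4 % | (0.074 − 0.054)/0.946 = 2.1 % | 0.074/0.946 = 7.8 % |

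Because b exceeds f in each row, the loss cannot be zero on a common denominator. For student WEMWBS, 3,600 × 0.891 = 3,208 students are followed up. Of these, 3,208 × 0.148 ≈ 475 are lost under independence, with a range of 3,600 × 0.039 ≈ 140 to 3,600 × 0.148 ≈ 533.

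**Precision for students.** Under independence the adjusted WEMWBS model uses 0.852 × 0.891 = 75.9 % of students, against 89.1 % unadjusted. Per school that is m = 113.9 against 133.7. The variance of an arm mean is proportional to (1 + (m − 1) × ICC)/m. No student ICC is given, so the values below are borrowed from the teacher WEMWBS sample size section.

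| Assumed ICC | m = 113.9 | m = 133.7 | Variance ratio | SE ratio |
|---|---|---|---|---|
| 0.01 | 0.01869 | 0.01741 | 1.07 | 1.04 |
| 0.02 | 0.02861 | 0.02733 | 1.05 | 1.02 |
| 0.05 | 0.05834 | 0.05711 | 1.02 | 1.01 |

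For SDQ (0.838 × 0.873 = 73.2 %, so m = 109.7 against 131.0) the variance ratios at ICC 0.01 and 0.05 are 0.01902/0.01756 = 1.08 and 0.05866/0.05726 = 1.02, which give the same 1 % to 4 % in standard error.

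These ratios isolate the loss of people. They leave out whatever precision baseline adjustment itself brings. They are also a ceiling on what the fix recovers for a given loss, because a student with a filled-in baseline gains nothing from the adjustment.

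**Teacher PHQ-8, side by side.** The opening of Secondary analyses reads as baseline-as-covariate. The PHQ-8 paragraph names outcomes measured at 12 and 24 months and promises inclusion on one observation. Primary analysis, by contrast, lists baseline among the repeated measures of WEMWBS, so there the one-measure rule works. The PHQ-8 paragraph does not say which structure it follows.

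**The case against.** The strongest points on the other side, and what is left of each:

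- **The one-observation rule does not govern students.** This stands. A reader might infer that the student loss of about 15 % contradicts that rule, but the rule sits only in the paragraph on outcomes measured at 12 and 24 months. The student point is an unstated handling rule. The relevant figure for the conflict is 7.4 %, for teacher PHQ.
- **The PHQ-8 conflict depends on one reading.** This also stands. If baseline is a repeated outcome, as in the primary model, nobody with an observation is dropped. The text leaves this open, so the conflict is conditional.
- **Complete-case analysis is nowhere stated, and covariate handling may be left to an analysis plan that is not shown.** Fair, which is why the point concerns a default fit. It survives because the article itself sets out an unadjusted-then-adjusted sequence and gives imputation only the role of a repeat.
- **Imputation would bring these students back.** True if multiple imputation is used. The commitment to assess missing data with an imputation model is firm and only the choice of method is conditional, but the main adjusted estimate is still the one without imputation.
- **No bias is shown.** Correct. A reader might infer a biased arm effect, but Randomisation places allocation after baseline collection, so among students enrolled by then the arm cannot have caused a missing baseline.

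**Conclusion.** The point holds as a modest, inexpensive improvement to the secondary analyses. For students, a default fit of the adjusted 24-month regression loses 14.8 % of followed-up students for WEMWBS (4.4 % to 16.6 %) and 16.2 % for SDQ (4.0 % to 18.6 %). The consequence is a sequence of models fitted to different samples and, for WEMWBS, a variance about 2 % to 7 % higher. For teacher PHQ-8, baseline as a covariate cannot be squared with the one-observation rule, and 7.4 % (2.1 % to 7.8 %) of followed-up teachers would be affected.

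The central figures rest on independent missingness across waves, the ranges on a common denominator, and the precision figures on borrowed teacher ICCs. People who join after baseline would add to the loss, but no figure is given for them. The primary analysis is unaffected.

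**What to change.** 1. **Student WEMWBS and SDQ (linear models).** Define one analysis set: students enrolled at allocation who have a 24-month score. Where baseline is missing, fill it with the overall mean across both arms and add a missing-baseline indicator. Fit the unadjusted and adjusted models to that same set. Restricting to students enrolled at allocation matters, because the argument that arm cannot affect baseline missingness does not extend to later joiners. Keep multiple imputation as a sensitivity analysis for missing follow-up scores.
2. **Teacher PHQ-8.** State that baseline is modelled as one of the repeated outcomes, as in the primary analysis, with the arm contrast taken at the follow-up occasions, and that the baseline-covariate step does not apply. The one-observation rule then holds as written.

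The cost is a few sentences of analysis text and slightly more programming. No data collection changes.
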